### Intervention

The intervention will consist of the 8-week Mindful Awareness and Resilience Skills for Adolescents (MARS-A) program [23,37], an evidenced-informed in-person MBI adapted specifically for youth with chronic health conditions. This program was developed by coauthors DV and JL at British Columbia Children’s Hospital and the University of British Columbia. MARS-A is based on 3 established evidence-based MBIs for adults and adolescents: mindfulness-based stress reduction (MBSR) [6,38], mindfulness-based stress reduction for teens (MBSR-T) [13], and MBCT [39,40]. The content of the program will be the same for in-person and eHealth groups with only minor adjustments for the eHealth group to allow all participants to remain in view of their Web camera during the sessions. All participants will be offered eight 90-minute weekly evening sessions—this represents an adaptation from adult MBSR and MBCT sessions which are typically 150 minutes in length—led by 2 experienced mindfulness providers with committed daily meditation practices (for this study, coauthor NC with the assistance of coauthor EW), who have been trained in facilitating MARS-A and who will also adapt the program for the online group. Also, while the MARS-A program usually includes a silent half-day retreat, this will not be included in the intervention so as not to disadvantage participants in the eHealth group for whom it might not be feasible to create a silent environment for a longer period of time. Sessions will include short meditation practices, breathing exercises, guided discussion (mindful inquiry), and mindful movements adapted to the context of chronic illness. All participants will also receive a copy of a self-help book for adolescents, *The Mindful Teen: Powerful Skills to Help You Handle Stress One Moment at a Time* [37] (by coauthor DV), to encourage regular practice and maintenance of newly acquired mindfulness skills. Every session will start with a brief review of home practice and will close with a discussion of the home practice for the following week. Participants will receive a weekly reminder email before each session to encourage them to complete home practice exercises and to remind them about the date and time of the next in-person or online mindfulness session. A summarized thematic overview of the MARS-A program can be found in Table 3.

Participants in the in-person groups will meet at the hospital in a designated teen-friendly room containing chairs and yoga mats. Sessions will take place once a week after school from 5:30 PM to 7:00 PM. Participants will have a 5-minute break at the middle of each session, and a snack will be provided.

Participants in the eHealth groups will be encouraged to find a quiet room with as little outside noise and distraction as possible. They will be required to have access to the Internet, a desktop or laptop computer equipped with a webcam or a tablet or mobile phone with webcam function. Participants and facilitators will be connected using the secure password-protected audio-visual platform Zoom Video Conferencing allowing up to 50 different computer connections. With this interface, participants and instructors can see and hear each other and interact in real time. This interface also allows for audio and video recording of mindfulness sessions and allows hosts to restrict access to meeting members who might not behave appropriately during sessions. All in-person and eHealth mindfulness sessions will be recorded and reviewed by a clinical psychologist with experience and expertise in mindfulness for adolescents (coauthor CMH) to ensure delivery of similar content between groups.

**Table 3 table3:** Thematic overview of the Mindful Awareness and Resilience Skills for Adolescents curriculum.

Week	Theme	Content
1	Stress, Depression and Health—Introduction to Mindfulness for Adolescents	Introduction to mindfulness and group expectations Introduction to stress and depression Group and home practices: breathing practice, sitting meditation, and the body scan
2	Foundations of Mindfulness	Developing a practice Key elements of mindfulness Group and home practices: body scan, mindful eating, sitting meditation
3	Informal Mindfulness Practice and Gratitude	Introduction to informal mindfulness practice Gratitude and pleasant events Group and home practices: mindful movement, 3-minute breathing space, walking meditation
4	Unpleasant Experiences, Physical Sensations, Physical Pain	Discussion: making peace with pain, suffering, and unpleasant physical sensations Group and home practices: mindful stretching, 3-minute breathing space, body scan
5	Seeing Thoughts as Thoughts	Cognitive exercise: thought distortions Discussion: mindfulness of thoughts, rumination Group and home practices: sitting meditation, short breathing practices
6	Handling Emotions	Discussion: handling emotions Group and home practices: mindful stretching, walking meditation, 3-minute coping space
7	How to Best Take Care of Yourself	Discussion: taking care of yourself Developing an action plan for future practice Group and home practices: loving-kindness meditation, sitting meditation, 3-minute coping space
8	Continuation of Practice	Course review and evaluation Discussion: maintaining a practice End of course celebration Group practices: mindful stretching, silent sitting, 3-minute breathing space

All participants will be invited to complete daily mindfulness meditation exercises at home. Participants will be asked to fill a practice log tracking the type, duration, and frequency of individual mindfulness home practice at the beginning of each mindfulness session using the TickIT online platform used for research questionnaires.

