All interviews will take place through the Zoom electronic audio-visual platform and will be led by a female research assistant, coauthor CV (MD). The research assistant will use an interview guide adapted from a study led by coauthor SAK [33]. She will be encouraged to take field notes during the interviews and will have received individual training in conducting semistructured interviews by coauthors EW (MEd) and SAK (PhD), who both have experience leading semistructured interviews and focus groups with youth. Participants will complete the interview in a private room, at home, with no other nonparticipants or researchers present and will be informed that the research assistant is a medical doctor, has limited experience with mindfulness, and has interest in understanding the effects of mindfulness in adolescents with chronic medical conditions. The research assistant will have met with each participant at baseline either in-person or virtually through the Zoom platform for a recruitment meeting. Recordings will be password-protected and only the research assistant (who will also be transcribing the recordings) will have access to them. Transcriptions will be de-identified using a patient code available only to the research assistant. Transcripts will be returned to participants for comment and correction if there is ambiguity at the time of analysis. Data will be analyzed using a grounded theory model [34] until data saturation is reached. Data for secondary outcomes will be collected for all participants. It is expected that research questionnaires will take 15 to 20 minutes to complete.

Saliva samples for cortisol analysis will be drawn at wake-up, at 12:00 PM, at 5:30 PM, and at 7:00 PM on the first and eighth (last) MBI session to capture fluctuations in cortisol levels throughout the course of the day. Participants will receive a reminder phone call the day before each saliva sampling occurs. This will allow for the comparison of pre-post cortisol level differences between participants in the in-person and eHealth arms. Participants in the eHealth arm will be provided with prepaid postage for return of saliva samples, which they will be able to send from home. It has been shown that saliva samples can be exposed to room or exterior temperatures for at least 72 hours without affecting cortisol values [35]. Once received, saliva samples will be kept frozen until they are sent to a specialized laboratory for analysis by enzyme immunoassay [36].

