## Discussion

### Anticipated Results

Based on previous pilot data collected by our team [11,15,23,25], we anticipate excellent levels of feasibility, acceptability, and satisfaction among participants in the in-person groups. In a study by [name] and colleagues [15] conducted in 19 adolescent females with chronic pain, using a similar MBI, the rate of attrition was low (17%), attendance was high (84%), and participants reported positive changes in the way they coped with their condition. We anticipate similar results in the eHealth groups, based on data from adult studies [18]. We hypothesize that both the in-person and eHealth modes of delivery will provide similar and significant improvements in mindfulness skills, mood, anxiety, self-esteem, and illness perception when compared to wait-list controls and that the magnitude of these effects will be correlated with the regularity of home practice. We project that participants in in-person and eHealth groups will have similar levels of home practice. In addition, we anticipate a significant reduction in pre-post session (5:30 PM to 7:00 PM) stress levels for both in-person and eHealth groups. Finally, we anticipate that all participants will see benefits of having incorporated mindfulness in their everyday life, such as improved level of functioning, sleep, or coping with illness, which will be captured by our semistructured interviews.

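### The 5:30 to 7:00 PM cortisol fall, taken alone, cannot be credited to the MBI, and comparing it raw between arms mixes delivery mode with an in-person snack

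*Protocol article*

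**What the plan says.** The Data Collection section of the protocol article sets four saliva samples a day, "at wake-up, at 12:00 PM, at 5:30 PM, and at 7:00 PM on the first and eighth (last) MBI session", to follow cortisol as it varies over the day and to compare pre-post differences between arms.

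The Intervention section gives the in-person hours: "Sessions will take place once a week after school from 5:30 PM to 7:00 PM". The same paragraph adds: "Participants will have a 5-minute break at the middle of each session, and a snack will be provided". The eHealth paragraph that follows mentions no snack.

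Table 1 places cortisol at time 0 and week 8 for the early groups, and at weeks 8 and 16 for the wait-list groups, whose MBI begins at week 8.

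Under Anticipated Results the authors write: "we anticipate a significant reduction in pre-post session (5:30 PM to 7:00 PM) stress levels for both in-person and eHealth groups". Under Outcome Measures the reason for choosing cortisol is different. It is to reproduce a pilot in which the reduction during a session became larger from before to after the MBI.

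On sample return: "Participants in the eHealth arm will be provided with prepaid postage for return of saliva samples, which they will be able to send from home". The protocol supports this by citing evidence that "saliva samples can be exposed to room or exterior temperatures for at least 72 hours without affecting cortisol values".

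**The concern.** There are two separate problems with the evening pair.

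The first is the missing comparator. Cortisol varies over the day, which is the protocol's own reason for sampling four times. A change between 5:30 and 7:00 PM on a session day therefore combines any effect of the session with whatever would have happened in those 90 minutes anyway. If levels tend to drop at that hour, a significant reduction appears without any session effect. If they tend to rise, a real effect is masked.

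The second is unequal conditions. The in-person groups are given food between the two swabs and the eHealth groups are not. If eating moves the 7:00 PM value, the fall differs between arms for a reason unrelated to stress or to how mindfulness is taught.

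At stake is the reading of one stated secondary outcome: a drop reported as stress reduction, or a difference between arms reported as an effect of delivery mode.

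**Working it through.** The plan gives no cortisol SD, no evening slope, no snack effect and no cortisol power figure, so there is no figure to reproduce. The first two steps follow from the text. Steps 3 to 5 use assumed effect sizes, in SD units of the individual 5:30 to 7:00 PM fall.

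**1. Is any evening pair taken without a session?** Data Collection ties sampling to the first and eighth sessions. In Table 1 the wait-list groups have no cortisol at time 0, and their first sample is at week 8, when their own MBI begins. So none is. With 60 participants and two sampling days there are up to 60 × 2 = 120 evening pairs, all on session days.

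**2. Does the snack fall between the swabs?** The in-person session runs from 5:30 to 7:00 PM, the swabs are at 5:30 and 7:00 PM, and the break is mid-session. So it does, for up to 30 × 2 = 60 in-person pairs. The wake-up and noon samples come before both session and snack.

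**3. Raw fall with zero MBI effect.** Let the background fall be d SD. The chance that a paired t test declares a fall is P = 1 − F(t₀.₉₇₅,ₙ₋₁; n − 1, d√n), where F is the noncentral t distribution function. For d = 0.5 and n = 30 the noncentrality is 0.5 × √30 = 2.74 and P = 75%. The protocol expects 10% to 20% attrition, so n = 30 × 0.9 = 27 and 30 × 0.8 = 24 are also shown.

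| Assumed background fall | n = 30 | n = 27 | n = 24 |
|---|---|---|---|
| 0 | 2.5% | 2.5% | 2.5% |
| 0.2 SD | 18% | 17% | 15% |
| 0.35 SD | 46% | 42% | 38% |
| 0.5 SD | 75% | 71% | 65% |
| 0.8 SD | 99% | 98% | 96% |

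**4. Raw comparison of the session-8 fall between arms.** Assume the snack shifts the in-person fall by 0.5 SD and delivery mode has no effect. With 30 per arm the noncentrality is 0.5 × √(30/2) = 1.94. In three sets of 4,000 simulated trials, a two-sided 5% test found a difference in 46% to 49%.

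**5. Change in the fall from session 1 to session 8.** Write b for the background fall, q for the snack shift and m for any change in the fall due to the MBI. The in-person fall is b − q at session 1 and b − q + m at session 8, so the difference is m. The eHealth fall is b, then b + m, and again the difference is m. Constant b and q cancel. With m = 0 the same simulations rejected in 4.6% to 5.0% of trials within an arm and 4.7% to 5.2% between arms, close to the nominal 5%.

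The cancellation needs b and q to be equal on both evenings. Table 3 lists an end-of-course celebration in week 8. It does not say food is served, but equal eating conditions cannot be taken for granted.

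**The case against.** The strongest reply is that the raw fall is one sentence in the Discussion and not a specified endpoint. Data Collection already plans a pre-post comparison between arms, and Outcome Measures already names the change in the within-session fall as the finding to reproduce. A cortisol analysis may be set out in an SAP that is not shown. This largely stands, and it limits the point to the anticipated result and to any raw comparison of the evening fall. It does not answer the snack, which is written into the session schedule and can be neutralised only before sampling.

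One can also say that the snack belongs to in-person delivery, and that nothing shows eHealth participants do not eat at home at that hour. The second part is fair, and the size and direction of the imbalance are unknown. On the first part, a cortisol shift caused by food is still not a stress difference. The protocol also aims to keep the arms alike: it drops the half-day retreat so as not to disadvantage the eHealth group.

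Two stronger readings are tempting, and the documents support neither.

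- A reader might infer that no cortisol result can be attributed to the MBI or its mode. The wake-up and noon samples precede session and snack. The session-1 to session-8 change removes constant background and snack effects. At week 8, Table 1 also gives a randomised contrast within each mode: early groups at session 8 against wait-list groups at session 1, at the same clock times and with the same snack and return arrangements. It cannot isolate the effect of sitting through one session, but it does bear on attribution to the MBI.
- A reader might infer that posted eHealth samples older than 72 hours are invalid and should be excluded. The cited stability is a lower bound, and nothing in the text shows degradation afterwards or late arrival. Exclusion would fall mainly on the mailed arm and create unequal missing data.

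**Conclusion.** The point holds for the evening pair only. The raw 5:30 to 7:00 PM fall has no no-session comparator and cannot be attributed to the MBI. Its raw comparison between arms mixes mode with a snack that the protocol provides to the in-person groups alone. Both statements follow from the text without any assumed effect size.

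The size is unknown. The 18% to 99% range (30 participants, background fall of 0.2 to 0.8 SD) and the roughly 48% for a 0.5 SD snack shift are illustrations. The documents say that cortisol fluctuates over the day, but not in which direction it moves in this window or by how much.

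The consequence is modest. Cortisol is a secondary outcome, and the MAAS-A noninferiority conclusion is not touched.

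**What to change.** - On the session 1 and session 8 evenings, offer the in-person snack after the 7:00 PM swab. Give both arms the same instruction on eating between the swabs, and record anyone who eats.
- Base the evening cortisol conclusion on the session-1 to session-8 change in the 5:30 to 7:00 PM fall, within and between arms. This is the pilot contrast that the protocol already cites.
- Reword the Anticipated Results sentence to match, and do not present the raw within-session fall as evidence of stress reduction.
- For the posted samples, at most log the time from sampling to freezing in both arms and use it in a sensitivity analysis, with no exclusion at 72 hours.

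The cost is a delayed snack on two evenings per group, one recorded item on eating, a time field if the optional log is kept, and a change of wording. No visits, samples or participants are added.

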### Outcome Measures

The primary outcome measure for this study is mindfulness skills acquisition, assessed by the Mindful Attention Awareness Scale for Adolescents (MAAS-A) [41]. This 14-item Likert-type scale has been previously validated in large samples of youth with chronic health conditions. Secondary outcomes will include quantitative and qualitative measures as detailed in Table 2: illness perception, mood and anxiety, self-esteem, cortisol levels (biological marker for stress) [42], individual practice, personal experience during the program, and facilitator feedback about adaptation of the MARS-A curriculum for the eHealth platform. The authors chose salivary cortisol levels as the biological marker for this study because of the possibility of using a noninvasive sampling method (ie, in comparison with blood tests) and based on promising, yet inconsistent reports of the effects of MBIs on cortisol levels and recommendations for future study [43]. They also chose cortisol in an attempt to reproduce the findings of a pilot study by [name] and colleagues [15] where reductions in cortisol levels during a mindfulness session had been shown to increase significantly pre- and post-MBI in a similar population of youth with chronic pain.

### Power Calculations

Sample size was determined on a realistic estimate based on recruitment rates from previous pilot studies. We estimate that 3 months will suffice to recruit 60 participants. With half the participants in the in-person groups and half the participants in the eHealth groups, the study will have 80% power of confirming noninferiority of the eHealth mode of delivery with a margin of 0.45 points on the MAAS-A scale. This margin reflects the change in MAAS-A scores found in the initial validation study of the MAAS in adolescents using an in-person program [41]. Unfortunately, the convenient sample size of 60 participants used for this study will not allow sufficient power to demonstrate noninferiority of secondary outcomes assessed by standardized questionnaires, based on recent mindfulness studies using these measures in adolescent populations [44,45].

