### Recruitment and Enrollment

Recruitment for this study will primarily take place in outpatient clinics of a tertiary care pediatric hospital when patients arrive for their scheduled initial or follow-up appointments. Participants will be referred for inclusion in the study by a member of their health care team after discussion with the patient and family. Nurse practitioners and social workers will also screen clinic lists to proactively identify potentially eligible participants. Brief presentations of the study will occur at divisional rounds and with small groups of health providers to increase awareness about the study. Posters and brochures will be distributed throughout clinics and offices.

Recruitment will occur until a convenient sample size of 60 participants is reached or until a maximum of 3 months of active recruitment has occurred (whichever happens first). Based on the results of a pilot study performed by our research team with 19 female adolescents with chronic pain [15], we anticipate that a period of 3 months will be sufficient to enroll the targeted number of participants (average enrollment rate: 5 participants per week).

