### Attrition and Compliance

Based on the results of a pilot study by [name] and colleagues [15], we expect attrition rates to be low (between 10% and 20%) and compliance (attendance for mindfulness sessions) to be high, with a mean attendance rate of 6 to 7 sessions out of 8. To our knowledge, no study examining 8-week MBIs delivered via eHealth in adolescents is currently available. Extrapolating from studies conducted in adults [22,28], we anticipate that attrition rates will be comparable for in-person and eHealth groups.

Participants having completed at least 4 of the 8 mindfulness sessions will be considered to have attended sufficiently to be included in data analysis. Pilot data on individual home practice suggests that participants will be practicing between 2 and 10 times per week for a median duration of 8 minutes per practice [15].

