### Data Analysis

Quantitative and qualitative data analysis will take place as described in Table 2. All quantitative analyses will be conducted using SPSS 24th edition (IBM Corp). Descriptive statistics will be used to identify participant demographics and disease characteristics. Quantitative self-report data will be analyzed using 1-way analyses of variance and analyses of covariance as well as paired *t* tests to assess pre-post MBI changes and to compare outcomes in the in-person versus eHealth arms as well as between the early versus wait-list control groups. A margin of 0.45 will be used as a prespecified noninferiority margin. For the primary outcome (mindfulness skills acquisition), the noninferiority question will be based on a confidence interval of 95% (2-sided) in relation to the noninferiority margin for the different treatment groups.

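### The 80% power is stated for 60 recruited participants with no allowance for the plan's own 10-20% attrition; at the expected analysed number it is about 76% to 70%

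*Protocol article*

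**What the plan says.** The Power Calculations section starts from recruitment: "We estimate that 3 months will suffice to recruit 60 participants". It divides that number evenly between the two modes of delivery and, for the sample so divided, claims that "the study will have 80% power of confirming noninferiority of the eHealth mode of delivery with a margin of 0.45 points". In the same section the article concedes too little power for the secondary questionnaire outcomes, so the primary MAAS-A comparison is the one hypothesis presented as powered.

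The Attrition and Compliance section gives the expected loss, in percent: "we expect attrition rates to be low (between 10% and 20". It adds that only participants who complete at least 4 of the 8 sessions enter the data analysis. The Discussion reports 17% attrition in the team's pilot.

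The Recruitment and Enrollment section stops enrolment at 60, or after 3 months if that comes sooner. No section enlarges the sample for dropouts or replaces them.

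The Data Analysis section fixes the test. "A margin of 0.45 will be used as a prespecified noninferiority margin", and the conclusion rests on a "confidence interval of 95% (2-sided) in relation to the noninferiority margin".

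**The concern.** The power is tied to the number recruited, while the analysis will use the number retained. By the article's own expectation these differ by 6 to 12 people out of 60. If 80% is right for 30 analysed per arm, it cannot also be right for 24 to 27.

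The trial is described as preparation for a larger multicenter trial. If its confidence interval crosses the margin, readers will judge that result against the stated 80%. At the upper end of the expected attrition, the chance of an inconclusive result when the two modes are truly equivalent would be about 3 in 10 instead of 2 in 10.

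**Working it through.** **Inputs from the protocol article**
- Power 80%, 60 participants, half per arm, so 30 per arm (Power Calculations).
- Margin 0.45 MAAS-A points, 2-sided 95% confidence interval, which is one-sided 0.025 for noninferiority (Data Analysis).
- Attrition 10% to 20% (Attrition and Compliance). 60 × 0.90 = 54, or 27 per arm; 60 × 0.80 = 48, or 24 per arm.

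**Assumptions of this check**
- True difference between arms is 0. The Discussion expects similar improvement in both.
- Comparison of two means without baseline adjustment.
- Attrition equal in the two arms, as the article anticipates.

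**Step 1: the plan's own figure.** The article gives no standard deviation, so the 80% cannot be reproduced independently. It can be taken as given and solved for the SD that it implies. In the normal approximation,

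n per arm = 2 × SD² × (1.960 + 0.842)² / 0.45².

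Setting n = 30 gives SD² = 30 × 0.2025 / (2 × 7.849) = 0.387, so SD = 0.622. With the noncentral t distribution the implied SD is 0.612.

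**Step 2: power at the expected analysed number.** With the SD held fixed, the standardised margin shrinks with the square root of n, so the SD cancels:

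power(n) = Φ( 2.802 × √(n/30) − 1.960 ).

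- n = 27: 2.802 × 0.949 − 1.960 = 0.698, power 75.7%.
- n = 24: 2.802 × 0.894 − 1.960 = 0.546, power 70.7%.

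**Step 3: the same with the noncentral t** (SD 0.612, degrees of freedom 2n − 2).

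| Analysed per arm | Attrition | Power |
|---|---|---|
| 30 | none | 80.0% |
| 27 | 10% | 75.6% |
| 25 | about the pilot's 17% | 72.2% |
| 24 | 20% | 70.4% |

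The two methods agree to within half a percentage point.

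**Step 4: the alternative reading.** If the 80% had been meant for 27 or 24 analysed per arm, the implied SD would be 0.579 or 0.545 (t), and power with all 60 analysed would be about 84% or 88%. The article does not say this.

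**The case against.** The strongest reply is that the article nowhere says that the 80% assumes 60 analysed. It gives neither the SD nor the model, and it condenses a fuller protocol that is not shown. That stands in part: 30 per arm is the plain reading, not an explicit statement, and the missing SD is a detail that an article may leave out. But the point does not rest on the omission. The article attaches a number to the recruited sample and gives an attrition figure that does not fit it.

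A second reply is that analysis of covariance is among the listed methods and could recover the loss. It could. If the 80% was an unadjusted figure and the SD is 0.612, an assumed baseline-to-follow-up correlation of 0.3, 0.4 or 0.5 gives about 74%, 78% or 82% at 24 per arm, and about 79%, 83% or 87% at 27. The article gives no such correlation and does not say which listed method serves the primary comparison, so this shows what could be claimed, not what has been. If the 80% already includes adjustment, the drop from attrition is as computed.

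A third reply is that the sample size was set by recruitment capacity and funding, that the Strengths and Limitations section admits the small sample, and that no decision rule uses the 80%. All true, and it limits the weight of the point. It does not make the figure fit, because the admission of insufficient power covers only the secondary questionnaire outcomes.

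**Conclusion.** The point holds as a statement that the plan's own figures do not support. At the expected 10% to 20% attrition, power for noninferiority is about 76% to 70%, not 80%. This rests on four things: 80% being correct for 30 per arm, an unadjusted comparison, the 2-sided 95% interval, and no true difference. It does not rest on any particular SD. It is a correction to one sentence and does not threaten the design or the validity of the noninferiority test, which depends on the interval and the margin.

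A reader might infer more, and the documents do not support it:
- *That the 80% was computed at a looser significance level than the planned interval.* The only level in the article is the 2-sided 95% interval.
- *That the 4-of-8-session rule removes a further group on top of attrition.* The article does not say that the two losses add up, and those who leave may largely be those who attend too few sessions.
- *That the 3-month limit contradicts the power statement.* That statement is conditional on 60 participants, and the article expects to reach 60 in time.
- *That delivery in groups lowers power by a known amount.* The article gives no figure from which to calculate one.

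**What to change.** Restate the power sentence for the number expected in the analysis, for example: *With 48 to 54 of 60 participants analysed, power to show noninferiority at a margin of 0.45 with a 2-sided 95% confidence interval is about 70% to 76%.*

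If the 80% already refers to analysed participants, or to a baseline-adjusted model, say so and give the figure on that basis with its assumptions.

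The cost is one sentence and possibly a less favourable stated figure. No change to enrolment, margin or analysis is needed. For scale only, holding 80% at 60 analysed would take 60 / 0.90 = 67 to 60 / 0.80 = 75 randomised, which is not asked for in a sample fixed by capacity and funding.

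### The 0.45-point noninferiority margin equals the in-person change it was taken from, so meeting it guarantees no preserved benefit and cannot show that eHealth is comparable with in-person delivery

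*Protocol article*

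**What the plan says.** The Power Calculations section of the protocol article claims that "the study will have 80% power of confirming noninferiority of the eHealth mode of delivery with a margin of 0.45 points on the MAAS-A scale", and explains the size of the margin in a single sentence: "This margin reflects the change in MAAS-A scores found in the initial validation study of the MAAS in adolescents using an in-person program". The Data Analysis section makes it the decision rule: "A margin of 0.45 will be used as a prespecified noninferiority margin", and "the noninferiority question will be based on a confidence interval of 95% (2-sided) in relation to the noninferiority margin".

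No section gives a fraction of the effect to be preserved, a minimal important difference, or a clinical reason for accepting a loss of 0.45. Study Design and Data Analysis provide for comparing early with wait-list groups, but the noninferiority decision does not depend on that comparison. Strengths and Limitations describes the hypothesis under test as the two modes being comparable in teaching mindfulness content and skills.

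**The concern.** A noninferiority margin states how much of the active comparator's effect may be given up. Here the only stated basis for the margin is the effect itself. If in-person delivery again produces a change of 0.45, a lower confidence limit just inside -0.45 excludes only the loss of all of it. That is evidence that eHealth does better than no change. It is not evidence that eHealth teaches the skills about as well.

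The primary decision rule therefore cannot carry the primary claim. The abstract and the discussion link a successful result to wider use of eHealth for adolescents who cannot attend in person, so a positive finding could be taken as support for a mode that has lost a third or a half of the effect. The advertised 80% power also depends on the width of this margin.

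**Working it through.** **Inputs from the protocol.** Margin 0.45. Two-sided 95% CI, so one-sided alpha 0.025. Power 80%. Total 60 ("We estimate that 3 months will suffice to recruit 60 participants"), split equally ("With half the participants in the in-person groups and half the participants in the eHealth groups"), so 30 per arm. Attrition 10% to 20% (Attrition and Compliance). 

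**Assumptions.** The true difference behind the 80% is not stated and is taken as 0. No SD is given, so the 80% cannot be reproduced independently, and the SD it implies is solved for instead.

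**1. Preserved fraction.** Margin / reference change = 0.45 / 0.45 = 100%. Guaranteed preserved fraction = 0%.

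**2. SD implied by the stated power.** SD = 0.45 × √(30/2) / (1.960 + 0.842) = 1.743 / 2.802 = 0.622 by the normal approximation. The noncentral t version gives 0.612.

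**3. What passes at that precision.** SE = 0.622 × √(2/30) = 0.161. The 95% half-width is 1.96 × 0.161 = 0.315. The largest observed eHealth deficit that passes is 0.45 - 0.315 = 0.135, which is 30% of 0.45.

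**4. Chance of declaring noninferiority.** P = Φ((0.45 - true loss)/0.161 - 1.96). The t version agrees to the nearest percent.

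| True situation | True loss | P(declared noninferior) |
|---|---|---|
| No loss | 0 | 80% |
| Loses one third of 0.45 | 0.15 | 46% |
| Loses half | 0.225 | 29% |
| Keeps 25% | 0.3375 | 10% |
| Keeps 10% | 0.405 | 5% |
| Keeps none, in-person effect 0.45 | 0.45 | 2.5% |
| Keeps none, in-person effect 0.30 (assumed) | 0.30 | 15% |
| Keeps none, in-person effect 0.20 (assumed) | 0.20 | 34% |

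**5. Power at a half-effect margin (0.225).** Φ(0.225/0.161 - 1.96) = 29% with 30 per arm. With baseline-adjusted ANCOVA the SD is multiplied by √(1 - r²), taking the implied SD as that of an unadjusted score: 37% at r = 0.5 and 42% at r = 0.6. With 24 per arm (20% attrition) the unadjusted figure falls to about 24%. About 118 per arm would be needed for 80%.

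**6. Sensitivity to the SD.** For assumed SDs from 0.5 to 1.0 with 30 per arm, power at margin 0.45 runs from 94% to 41%, and at 0.225 from 41% to 14%.

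**7. Early eHealth versus pooled wait-list at week 8.** Table 1 shows both wait-list groups still untreated up to week 8, with questionnaires collected then, which gives 15 against 30. SE = 0.612 × √(1/15 + 1/30) = 0.194. Power for a difference of 0.45 is about 62% unadjusted (t, 43 df) and about 75% with ANCOVA at r = 0.5. Requiring both this and noninferiority at 0.45 gives joint power of about 55% by simulation, with full eHealth benefit and no attrition.

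**The case against.** The strongest reply is about practical risk. A reader might infer that the trial is likely to pass an eHealth program that keeps almost none of the benefit. The figures do not support that: an observed deficit above about 0.135 fails, and an arm truly keeping 10% of a 0.45 effect passes about 5% of the time. What stands is that the rule excludes no more than a total loss, and that losses of a third or a half pass quite often.

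A reader might also infer that this in-person arm is a cut-down version of the program behind the 0.45, and so must have a smaller effect. The Intervention section says that "while the MARS-A program usually includes a silent half-day retreat, this will not be included in the intervention", but that is a comparison with usual MARS-A, and the 90-minute sessions are compared with adult programs. Neither is compared with the program in the cited validation study, so the inference should not be made. Youth with previous MBI experience are eligible, but the direction in which that moves the effect is not established.

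The reference effect is only partly visible. Reading *reflects* as *equals* is fair but cannot be checked, and the text does not say whether 0.45 is a pre-post or a controlled change. If it is uncontrolled, the effect over control could be smaller and the margin could exceed it.

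Two further points are true but do not repair the rule. Comparisons with wait-list are already planned, so evidence on whether eHealth works will exist. And the trial is small and is presented as preparation for a multicenter study, which favours reporting an estimate rather than claiming noninferiority.

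**Conclusion.** The point holds as a fault in how the margin is justified and in what may be concluded from it. The margin equals the only effect cited for it, no other reason for tolerating such a loss is offered, and noninferiority is not conditional on anything else. Meeting the rule would show that the whole cited change has not been lost, and no more.

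The 0% preserved follows from the protocol's wording alone. The probabilities rest on the back-solved SD of 0.61 to 0.62, 30 analysed per arm and a normal outcome. The 15% and 34% figures rest also on assumed in-person effects of 0.30 and 0.20. The documents make a smaller effect possible but do not show it.

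**What to change.** Set the margin at a stated fraction of the cited change and give the reason for that fraction. Half, 0.225, is an example; the documents contain no fraction of their own. Because data collection is under way, record the change as made before any unblinded analysis. Restate the power at the new margin, with the SD and any baseline correlation given explicitly and allowing for the expected attrition.

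Make the primary conclusion the eHealth minus in-person difference in MAAS-A with its 95% CI, offered as input to the planned multicenter trial.

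If 0.45 is kept, say that meeting it rules out only loss of the whole cited change, and do not describe the modes as comparable. Report early eHealth against the pooled wait-list groups at week 8 beside it, as evidence only that eHealth works. Beating wait-list preserves no fraction of the in-person effect either, so it cannot license the stronger wording.

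The cost is a change of wording and a restated power figure. No added participants, visits or questionnaires are needed. The downside is real: at 0.225 the planned 60 participants give about 29% power instead of 80%, so a formal noninferiority conclusion becomes unlikely.
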